### Statistical analyses

In this study, the data analysis will be performed on the full analysis set (FAS), per protocol set (PPS) and safety analysis set (SS). The efficacy analysis will be conducted on an intention-to-treat (ITT) basis. The 95% confidence intervals (CIs) will be calculated as exact CIs. For the two primary outcomes, the *P*-value will be adjusted to 0.033. This value was based on a recommendation to divide the pre-specified *P*-value threshold by the value halfway between 1 (representing no adjustment) and the number of primary outcome comparisons (the denominator used for the Bonferroni correction) [23]. All statistical tests are 2-sided, and unless otherwise stated, *P* < 0.05 will be considered statistically significant. When the primary outcome measures are missing, the researchers will combine statistical analysis and clinical experience to judge whether to exclude the subject or replace the missing data with the last observation carried forward (LOCF).

The measurement data will be subject to normal distribution and homogeneity of variance, which is expressed as the mean ± standard deviation. Comparisons between groups will be performed using an independent 2-sample t test. Comparisons between multiple time points will be analysed using repeated-measures ANOVA, multivariate ANOVA or paired t test. When the data do not meet the criteria of normality and homogeneity, the results will be expressed as the median. The Wilcoxon rank sum test will be used to compare differences between groups. Before and after treatment, numerical variables and ordered categorical variables measured over multiple time points will be analysed using generalized estimating equations and a mixed effects model. The enumeration data will be expressed as frequency (n), constituent ratio (%) or ratio (%). If the variable data type is unordered, categorical comparisons between groups will be performed by the χ^2^ test. The ordered categorical variable data will be analysed using the rank sum test. Comparisons of two-way ordered data with different properties within contingency tables will be made with the linear chi-square test or rank sum test. Multivariate data analysis will be conducted using multiple linear regression, the K-M test, Cox regression or a trend test. All statistical analyses will be performed with IBM SPSS Statistics 24.0.

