### Statistical plan

#### Sample size calculation

The necessary sample sizes were calculated for the two primary outcomes, namely, the MoCA and MES. With reference to our previous study [21], the following parameters were used: the mean MoCA score (*μ*_r_) in the treatment group was 25.67; the mean MoCA score (*μ*_c_) in the control group was 23.36; we assumed that the superiority margin (Δ) was 1.20; the standard deviation (σ) was 2.21; the type I error rate (α) was set to the usual level, a unilateral value of 0.025), with Z_α/2_ = 1.96, the type II error rate (β) was set to a unilateral value of 0.05, with Z_β_ = 1.645; the ratio (K) of the treatment group size (*n*_1_) to the control group size (*n*_2_) was K = 1 (*n*_1_ = *n*_2_ = 104). Considering that there are three research centres in this study and a 20% dropout rate, the logistic regression analysis suggested that the sample size should be 15 to 30 times the number of indices being analysed plus an extra 30 patients, for a total required sample size of 280 patients (140 patients per group).

For the second primary outcome, we set the mean MES scores to 82.83 in the treatment group and 73.50 in the control group, with an SD of 7.83 [22]. We assumed that the superiority margin was 3.92 (1/2 standard deviation); we calculated that we would need a total of 122 patients (66 per group) to allow for a 20% dropout rate. Of the necessary sample sizes estimated for the two primary outcomes, the larger value was selected as the sample size for this study. The formula for calculating the sample size is as follows:

$$\begin{array}{c}{\mathrm n}_{\mathrm c}=\frac{\left({\mathrm Z}_{\displaystyle\mathrm\alpha/2}\;+\;{\mathrm Z}_{\mathrm\beta}\right)^2\;\mathrm\sigma^2\;\left(1+{\displaystyle\frac1{\mathrm k}}\right)}{\left(\mu_r-\mu_c-\mathit\triangle\right)^2}\\{\mathrm n}_{\mathrm r}={\mathrm{Kn}}_{\mathrm c}\end{array}$$

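### Testing MoCA and MES each at 0.033 is only a partial multiplicity correction (overall error up to about 6.6% if either may succeed), and it differs from the alpha used for the sample size

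*Protocol article*

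**What the plan says.** Under Statistical analyses, the protocol article sets one threshold for both primary outcomes: "For the two primary outcomes, the *P*-value will be adjusted to 0.033". The rule behind it is to divide the significance threshold by "the value halfway between 1 (representing no adjustment) and the number of primary outcome comparisons", with the Bonferroni denominator named as the other end of the range. A source is cited for the rule. The same section adds: "All statistical tests are 2-sided, and unless otherwise stated, *P* < 0.05 will be considered statistically significant". On intervals it says: "The 95% confidence intervals (CIs) will be calculated as exact CIs".

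Under Sample size calculation, the article says: "The necessary sample sizes were calculated for the two primary outcomes, namely, the MoCA and MES". There the type I error is "a unilateral value of 0.025", with a normal quantile of 1.96, and no adjustment for having two primary outcomes.

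The article does not say whether a positive trial needs one primary outcome or both. It gives no correlation between MoCA and MES.

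**The concern.** An adjusted threshold has a purpose only if a significant result on either outcome can support the efficacy claim. In that case a divisor of 1.5 instead of 2 leaves the overall false-positive rate above 5% unless the two test statistics are very strongly correlated.

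The alpha that decides the trial is also not the alpha that sized it, so the stated 95% power does not belong to the stated test. In addition, a 95% interval corresponds to p < 0.05. A primary result with p between 0.033 and 0.05 would have an interval that excludes the null value and yet would not be significant, and the article does not say which governs.

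**Working it through.** **Inputs.** From Statistical analyses: two primary outcomes, 0.033 each, two-sided. From Sample size calculation: MoCA means 25.67 and 23.36, margin 1.20, SD 2.21, z = 1.96 and 1.645, 104 per group, 20% dropout, 140 per group enrolled. Assumed here: correlations between the two test statistics from 0 to 0.9, since the article gives none.

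**1. The threshold reproduces.** The value halfway between 1 and 2 is 1.5, and 0.05/1.5 = 0.0333, printed as 0.033.

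**2. Overall type I error if either outcome counts.** If the statistics are independent, the error is 1 − (1 − 0.033)² = 6.49%, or 6.56% at the unrounded 0.0333. For correlated statistics it is 1 − P(|Z₁| < c and |Z₂| < c) under a bivariate normal distribution, with c = 2.132 for 0.033 and 2.128 for 0.0333.

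| Assumed correlation | At 0.033 | At 0.0333 |
|---|---|---|
| 0 | 6.49% | 6.56% |
| 0.3 | 6.35% | 6.41% |
| 0.5 | 6.08% | 6.14% |
| 0.7 | 5.61% | 5.66% |
| 0.8 | 5.25% | 5.30% |
| 0.9 | 4.72% | 4.77% |

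The error equals 5% at a correlation of 0.853 (for 0.033) or 0.862 (for 0.0333).

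**3. The sample size reproduces only at the unadjusted alpha.** The MoCA difference beyond the margin is 25.67 − 23.36 − 1.20 = 1.11. The article's formula gives (1.96 + 1.645)² × 2.21² × 2 / 1.11² = 103.03, rounded up to the stated 104. With z = 2.132 in place of 1.96, the same formula gives 114.

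**4. MoCA margin-test power.** Power = Φ(1.11/SE − z), with SE = 2.21 × √(2/n). With n = 104, SE = 0.3065. With n = 140 × 0.8 = 112, SE = 0.2953.

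| Two-sided alpha (z) | 104 per group | 112 per group |
|---|---|---|
| 0.05 (1.960) | 95.2% | 96.4% |
| 0.033 (2.132) | 93.2% | 94.8% |
| 0.025 (2.241) | 91.6% | 93.5% |

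**5. MES.** The net difference is 82.83 − 73.50 − 3.92 = 5.41, with SD 7.83. At alpha 0.025 and 112 per group, power is 99.8%, so MES does not limit the design.

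**The case against.** The article never claims 5% family-wise control. It presents 0.033 as a compromise fixed in advance, stricter than no adjustment and supported by a cited recommendation. How strictly to control multiplicity is partly a design choice. The excess also depends on an either-outcome success rule that is inferred. If both outcomes had to succeed, the error would be at most 3.3% and no adjustment would be needed. MoCA and MES both measure cognitive status, so some positive correlation is plausible. All of this stands, and it limits the weight of the point. It does not change the arithmetic: without a stated success rule or correlation, the article gives no basis for relying on 5%.

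The effect on power is small. With the planned 112 evaluable per group, 0.033 gives 94.8% against a target of 95%. The group comparison named under Statistical analyses is a plain two-sample t test without a margin. Against zero, the assumed MoCA difference is 2.31/0.2953 = 7.8 standard errors, so power is essentially 100% at any of these alphas. A reader might infer that the trial is underpowered or must enrol more patients. The figures do not support that.

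A reader might also fault the exact intervals. For a difference in means, the t interval is exact under the normality and equal-variance conditions that the article attaches to it, so that criticism fails there. Nor are 95% intervals beside an adjusted threshold wrong in themselves, since reporting them descriptively is common practice. What is missing is a statement that they do not decide the primary result.

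**Conclusion.** The point holds at moderate severity. If either outcome can carry the claim, the 0.033 rule allows an overall two-sided type I error of up to about 6.6%, and it reaches 5% only if the test statistics correlate at about 0.85 or more. This rests on the inferred success rule and on assumed correlations. It would go too far to say that the plan breaks a 5% guarantee, because the article makes none.

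The mismatch with the sample-size alpha needs no assumption about correlation. The stated 104 per group belongs to two-sided 0.05 and gives 93.2% MoCA margin-test power at 0.033. After allowing for dropout from 140 per group, the shortfall against 95% is only 0.2 percentage points.

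**What to change.** State that either primary outcome can support the efficacy claim, and replace 0.033 with Holm at an overall two-sided 0.05. Test the smaller of the MoCA and MES p-values at 0.025 and, if it is significant, test the other at 0.05. This holds the overall error at or below 5% whatever the correlation.

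Restate the MoCA margin-test power at the first-step alpha: 93.5% with 112 evaluable per group, against 96.4% at the alpha used for sizing. Keep the 95% intervals, label them as descriptive, and say that the Holm-adjusted p-values govern the primary decision. Setting 97.5% intervals for both outcomes would not work. A second-step p of 0.04 would be significant while its 97.5% interval included the null value.

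The cost is a few sentences, to be amended before the first unblinding. First-step MoCA power falls by 94.8 − 93.5 = 1.3 percentage points relative to 0.033, and by 96.4 − 93.5 = 2.9 points relative to the sizing alpha. In return, the second test is made at 0.05 instead of 0.033. Holding 95% MoCA power at 0.025 would take 120 evaluable per group (120/0.8 = 150 enrolled, against 140 planned). The small loss does not justify that, so no further patients are needed.

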#### Randomization

In this study, a stratified block randomization method will be used to divide the subjects in the same centre according to the "centre" first, and then subjects in the same centre will be divided into block randomization groups. This method not only ensures the balance of each known important prognostic factor but also ensures that the number of cases in each treatment group in each centre was close or equal; this method is also convenient for management. To ensure the comparability of the key factors affecting the prognosis of patients in the intervention or control group, the stratified factors considered in this study are centre, sex, age and TCM syndrome patterns. Block randomization requires that the research object of each block be a multiple of the number of groups (twofold or fourfold). The sample size of this experiment is 280 patients, so each group from each area should consist of 4 patients, for a total of 70 blocks. Among them, there were 35 (140/4) blocks from the Shanghai Municipal Hospital of TCM, 18 (70/4) blocks from Shanghai Jiading District Nanxiang Hospital, and 18 (70/4) blocks from the Shanghai Qingpu District Hospital of TCM. To reduce the loss of patients who meet the inclusion and exclusion criteria, the three centres could also set up a small number of blocks for 2 patients (such as fewer elderly patients) according to the actual needs.

At the same time, considering that when the three centres match patients of similar sex, age and TCM syndrome patterns into block groups, it is possible that the number of research objects in a block will be small or could lead to matching difficulties, so each centre should add 6 to 8 random participants (a total of 4 blocks).

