### Outcome evaluation

#### Baseline characteristics

Patients’ demographic characteristics including age, gender, ethnicity, marital status, cohabitation status, educational attainment, occupation, predisposing factors, prior therapies, history of illness, medication history, vital signs and weight for height will be considered. Baseline data for the enrolled participants will be recorded before randomization.

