#### Primary outcomes

Cognitive status will be evaluated with the MoCA and MES. The primary efficacy endpoints are the improvement rate for MoCA scores and MES scores, which will be measured before and after treatment in both groups. The MoCA has high sensitivity and specificity in distinguishing normal elderly individuals from those with MCI and mild Alzheimer's disease and can detect slight cognitive impairment [16]. The MES has been confirmed to be a valid and easily administered screening tool for MCI, and the score is independent of education and can also be used to evaluate individuals [17].

$$\text{Improvement rate} = \left[\left(\text{posttreatment score}-\text{pretreatment score}\right)/\text{pretreatment score}\right]\times100\%.$$

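### The stated between-group test adjusts for neither the baseline score nor the stratification factors, which costs precision and makes the test conservative but does not bias it

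*Protocol article*

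**What the plan says.** The Statistical analyses section of the protocol article gives a general rule for measurement data: "Comparisons between groups will be performed using an independent 2-sample t test". If normality or homogeneity of variance is not met, results are given as medians and "The Wilcoxon rank sum test will be used to compare differences between groups". Neither test is given a covariate or a stratum.

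The same section lists other methods. Numerical and ordered variables "measured over multiple time points will be analysed using generalized estimating equations and a mixed effects model". It adds: "Multivariate data analysis will be conducted using multiple linear regression, the K-M test, Cox regression or a trend test". None of these is tied to the primary endpoints or designated primary, and none names baseline score, centre, sex, age or syndrome pattern as a term.

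Under Primary outcomes: "The primary efficacy endpoints are the improvement rate for MoCA scores and MES scores, which will be measured before and after treatment in both groups". Each rate is computed as post minus pre, divided by pre, times 100%.

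Under Randomization: "the stratified factors considered in this study are centre, sex, age and TCM syndrome patterns". The purpose is given as "To ensure the comparability of the key factors affecting the prognosis of patients in the intervention or control group", so the protocol itself treats these factors as prognostic.

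Under Baseline characteristics: "Baseline data for the enrolled participants will be recorded before randomization". Table 1 schedules MoCA and MES at screening and at week 0.

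**The concern.** Stratified randomisation balances the arms on the strata, so stratum differences contribute little to the variation of the treatment contrast. An unadjusted t test still counts those differences in its standard error. If the strata predict outcome, as the protocol says they do, the standard error is larger than the design warrants.

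The baseline score is usually a strong predictor of a later cognitive score. The improvement rate brings baseline in through a fixed formula rather than with the weight the data support. A chance difference between arms at week 0 is therefore not handled as well as a covariate would handle it.

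The choice between the t test and the rank-sum test also depends on checks made on the trial data, so the primary method is not fixed in advance.

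At stake are interval width and some power, in a trial that already collects everything needed for adjustment.

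**Working it through.** **Inputs from the protocol article.** Sample size calculation: MoCA means 25.67 and 23.36, margin 1.20, SD 2.21, one-sided alpha 0.025 (z = 1.96), beta 0.05 (z = 1.645), 20% dropout, 140 per arm. Statistical analyses: threshold 0.033 for each primary outcome.

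**Inputs assumed, because the document does not give them.** The correlation r between baseline and week-8 score: 0.5 to 0.7, with 0.3 also shown. The share R² of outcome variance explained by the strata: 0.1 to 0.3. The SD is taken as 2.21 at both times.

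**1. The plan's own figure.** The net difference is 25.67 − 23.36 − 1.20 = 1.11. Then n = (1.96 + 1.645)² × 2.21² × 2 / 1.11² = 103.03, so 104 per arm, as stated. The formula takes no credit for baseline or strata. After 20% dropout, 140 × 0.8 = 112 per arm remain.

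**2. Baseline adjustment against a change score.** The document gives no SD for percentage change, so change in points stands in for it.
- Variance of change: 2σ²(1 − r). Residual variance after baseline adjustment: σ²(1 − r²). Ratio: (1 + r)/2.
- Standard error at 112 per arm: SD × √(2/112).

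| r | Variance ratio | SE, change score | SE, adjusted | Reduction in SE |
|---|---|---|---|---|
| 0.3 | 0.65 | 0.349 | 0.282 | 19% |
| 0.5 | 0.75 | 0.295 | 0.256 | 13% |
| 0.7 | 0.85 | 0.229 | 0.211 | 8% |

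**3. Ignoring the strata.** The true SE is the t-test SE × √(1 − R²). The actual two-sided type I error at nominal 0.05 is 2[1 − Φ(1.96/√(1 − R²))]. The check used 4,000 simulated trials per R² value, with 24 strata, blocks of 4 and 288 patients; the number of strata is an assumption.

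| R² | t-test SE too large by | Type I error, formula | Type I error, simulated |
|---|---|---|---|
| 0 | 0% | 0.050 | 0.051 |
| 0.1 | 5% | 0.039 | 0.039 |
| 0.2 | 12% | 0.028 | 0.030 |
| 0.3 | 20% | 0.019 | 0.022 |

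**4. Power of the unadjusted test on the plan's assumptions.** With SD 2.21 for the quantity compared, net difference 1.11 and 112 per arm, power is 96.4% at two-sided 0.05 and 94.8% at 0.0333. The target was 95%.

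**The case against.** **The t-test sentence is generic.** It is not labelled primary, and the sentence on generalized estimating equations and mixed models could be read to cover MoCA and MES, which Table 1 schedules at several visits. That is fair. But the primary endpoints are one before-to-after percentage per patient, for which the two-sample test is the natural reading. The repeated-measures and regression sentences also name no baseline or stratification term, so they do not supply the adjustment under any reading.

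**Baseline is already used.** This is correct. The improvement rate contains baseline in numerator and denominator, so it would be wrong to say that the plan ignores it. The right comparison is therefore with a change score. Comparing with a t test on the final score would suggest that the standard error falls from 0.295 to 0.211 at r = 0.7, but no such test is planned. The gain over a change score there is 0.229 to 0.211.

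**Covariate lists belong in the statistical analysis plan.** They often do, and one may exist. The point stands because the article states an unadjusted method. If a fuller plan adjusts, the published wording needs to agree with it.

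**Stronger readings that do not hold.**
- A reader might infer that a mismatched standard error makes the test invalid. It does not: the error is conservative, with type I error at or below nominal and no bias.
- A reader might infer that the trial is underpowered. Step 4 of the working does not support that, and power figures for a smaller true effect would rest on an effect size the document does not contain.
- A reader might infer that the rank-sum fallback removes an estimate in points needed for the 1.20 and 3.92 margins. A t test on a percentage gives no estimate in points either. That gap comes from the endpoint's scale, not from the fallback.

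**Conclusion.** The point holds as a matter of efficiency and should be corrected. The stated test uses baseline less well than covariate adjustment would and leaves out stratification factors that the protocol calls prognostic.

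Relative to a change score, the loss is about 8% to 13% of the MoCA standard error for r between 0.7 and 0.5. Separately, ignoring the strata overstates the standard error by about 5% to 20% for R² between 0.1 and 0.3. The two gains should not be added, since baseline score and strata may explain overlapping variance.

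The sizes rest on the assumed r and R², on equal SDs before and after, and on change in points standing in for percentage change. The direction does not depend on the exact values: in large samples adjustment does no worse than a change score, and ignoring prognostic strata makes the test conservative.

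The statement that power is adequate takes 2.21 as the SD of the quantity analysed. If 2.21 is instead the SD of a single score and r is as low as 0.3, an unadjusted change score has about 89% power at two-sided 0.05. That case strengthens the argument for adjustment, but the document does not establish it.

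**What to change.** Before the first unblinding described under Blinding method, name one primary model for each of MoCA and MES. This can be an ANCOVA, or the week-8 contrast of a mixed model for repeated measures, on the week-8 score or the change in points. Its terms are arm, week-0 score, centre, sex, age and TCM syndrome pattern. Use robust standard errors in place of the switch triggered by normality and variance checks, and keep the rank-sum test as a sensitivity analysis.

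The cost is small. The covariates are already recorded and no new data are needed. It is not purely a matter of analysis wording, however. Moving from improvement rate to points changes the endpoint as defined under Primary outcomes, so a short protocol amendment is needed. The Abstract and the Study design section already describe the outcome as change in score, so the amendment would also bring those descriptions into line.

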## Discussion

Population ageing is an inevitable trend for the world’s population [24], and China has one of the world’s fastest-growing demographics of older individuals worldwide [25]. It is estimated that by mid-century, the elderly population in China will reach 400 million, accounting for approximately 30% of the total population; accordingly, the prevalence of cognitive impairment in elderly individuals will increase. Shanghai was the first city to become a superaged society, in which ageing individuals constitute the highest percentage of the city’s population. The office of the Shanghai Working Committee on Ageing and the Municipal Bureau of Statistics recently released the latest data and showed that on December 31, 2019, there were 5.1812 million older adults aged 60 years and older, accounting for 35.2% of the total population registered in Shanghai, and 2729 older people were over 100 years old in Shanghai. In China, the population ageing problem has increased the number of individuals with incapacitating diseases, accounting for 3% of the total number of elderly people, which has led to substantial personal and social burdens [26]. Therefore, how can health problems brought about by population ageing be proactively addressed? Efficacious therapy and prevention strategies are urgently needed to cope with age-related neurodegenerative diseases, including cognitive impairment and dementia, which are difficult problems that we need to overcome in medical and health research [27].

Cognitive function involves various aspects of working memory, execution function, reasoning ability, verbal ability, and ability to perform activities of daily living [28]. Cognitive impairment refers to the impairment of one or more functions in the above areas, which can affect the social function and quality of life of patients to varying degrees and even lead to death in severe cases. MCI is a transitional state between normal ageing and dementia [29]. Cognitive impairment is not only a simple medical problem but also a serious social problem. To the best of our knowledge, the incidence rate of MCI is 6.7% at 60–64 years of age, and the prevalence rate is 10 to 20% in the elderly population over 65 years old and 25.2% in the population aged 80–84 years old [30]. More than half of MCI patients will progress to dementia within 5 years, and only a small number of MCI patients can maintain stable cognitive function or even return to normal [31]. Approximately 10% of MCI patients convert to Alzheimer's disease (AD) every year, and the incidence of dementia in MCI is 10 times higher than that in healthy elderly people [32]. Therefore, early intervention for MCI is very important for delaying the occurrence and development of dementia, improving the ability to perform activities of daily living, prolonging the survival period and reducing the burden of care and care; additionally, the early stage of MCI is considered to be the best intervention period to delay or reverse cognitive impairment.

Chinese herbal formulas have been widely used to improve cognitive function with a good curative effect. In the last few years, many investigators have engaged in research on TCM interventions in cognitive disorders to improve the management of MCI by TCM and to take the disease stage within the Alzheimer disease continuum seriously. TCM shows good clinical efficacy and characteristic advantages of early TCM intervention in cognitive impairment to provide an accurate basis to examine effective TCM therapies to delay the progression of cognitive impairment.

